### Targeted implementation of the SBB through state-specific programs

State health departments of NSW, QLD and VIC will promote the SBB initiative across all maternity services in their jurisdictions, however, initial rollout involves targeted support to hospitals recruited to state-specific SBB implementation programs. Commencement dates, recruitment strategies and implementation approaches differ across jurisdictions but the intent for all is to progressively embed the SBB within existing care over a 12-24 month implementation period (post-launching). Each jurisdiction nominated a division (within their health department) to oversee the implementation process and data collection as follows: Safer Care Victoria (SCV, VIC Government), Clinical Excellence Commission (CEC, NSW Government) and Clinical Excellence Queensland (CEQ, QLD Government). In their capacity as state health care quality and safety improvement agencies, they are responsible for recruitment of ‘targeted’ implementers, implementation of the SBB in these sites and data collection for the purposes of the process and impact evaluations.

A key strategy used to optimise uptake of the SBB is having a dedicated implementation (quality improvement) project team for each jurisdiction, led by health service executive leadership teams. These teams will provide support through to the end of the project with the aim to see changes incorporated into business as usual. They will provide leadership, generate and sustain motivation for change, provide tools to support practice change through education, audit and feedback, and benchmarking and implementation support forums to facilitate sharing of experiences of the SBB by clinical champions from across ‘targeted’ implementers. In each state, at least three implementation learning support forums will be conducted during the implementation period, bringing together local implementation teams to discuss successes and challenges to enhance implementation. The Stillbirth CRE study co-ordination team will provide wide-ranging support across the jurisdictional implementation programs through attendance and participation at learning forums and representation on project teams and high-level committees. During both implementation and maintenance phases of this study, the Stillbirth CRE will report annual benchmarking of selected indicators and support national forums to share learnings.

The SBB educational program covers each element of the bundle and includes both face-to-face skills development and eLearning. The first phase of the educational resources for healthcare professionals (eLearning) was officially launched in October 2019, by the Australian Federal Minister for Health. Complementary information and educational resources for women and their families have also been developed. These will further support implementation of the SBB in a way that meets women’s needs and include a public awareness campaign. The SBB Education Working Group, with representation from all major parent advocacy organisations and professional colleges, will provide guidance on the integration of the awareness campaign [28] with the state-led SBB implementation strategy in the antenatal clinic setting.

### Evaluation design

A mixed-methods approach will be used to assess the processes, impacts and outcomes for the SBB initiative. Change in rates for the primary clinical outcome, stillbirth rate at 28 or more weeks, will compare the pre-implementation rate (including longer term trends over 15 years) with the rate in the 2 year post-implementation period (Time Point 2 (TP2)), using routinely collected perinatal data (see Fig. 1.) To allow for differences in commencement dates between jurisdictions and implementation disruptions due to COVID-19 restrictions, a 2.5 year implementation period is proposed. Key process and impact measures will be compared pre- (baseline) and post-implementation at evaluation TP1 including data from surveys of women and healthcare professionals, clinical audits and implementation process data. A survey of maternity service leads will be undertaken at TP1 (post-implementation) to assess changes in maternity services resource use, level of implementation and the influence of leadership, governance and workforce culture on implementation.

**Fig. 1 Fig1:**
[figure not shown]
Study timeline and design. TP1- time point 1 (end of implementation period), TP2- time point 2 (2 years post-implementation)

### Evaluation measures

We will use a framework commonly applied to complex public health service research [29], adapted to suit this clinical context. This framework integrates process, impact, outcome and economic evaluations across different settings and stakeholder levels including: State level health regions, maternity service providers/hospitals, quality improvement leadership teams, maternity healthcare professionals and women receiving antenatal care. Both quantitative and qualitative methods will be used to collect measures across these settings (Fig. 2).

**Fig. 2 Fig2:**
[figure not shown]
Data collection tools used in the SBB program evaluation. This brings together data collected across different settings and stakeholders and indicates how these will contribute to process, impact, outcome, and economic evaluations. HCP- Healthcare professionals, NSW- New South Wales, QLD- Queensland, VIC- Victoria, SBB- Safer Baby Bundle

An adaptive evaluation approach to address the additional complexity of the impact of the COVID-19 pandemic on implementation and evaluation of the SBB is required. Evaluation measures and data collection tools may need amending in response to changing needs, priorities, constraints, and opportunities. Within the existing framework, the indirect impact of the COVID- 19 pandemic on SBB implementation across process, impact, outcome, and economic evaluations will need to be considered.

**Process measures** collected will assess the coverage, acceptability, feasibility, fidelity, and sustainability of the SBB program and its implementation at ‘targeted’ implementors across settings and for different stakeholders. These measures include; healthcare professionals experience and satisfaction with resources including completion rate of educational programs; women’s experience including acceptability of information materials and satisfaction with care; and for each element key measures indicating alignment of antenatal care practices with the SBB recommendations, Table 1.

**Table 1 Tab1:** Planned evaluation measures relating to the five elements of the Safer Baby Bundle

Element	Level of evaluation	Measure
Element 1: supporting women to stop smoking in pregnancy	Process	Proportion of women who are asked about their smoking status at first antenatal care visit and at 28 weeks antenatal appointment.
		Proportion of women who undertake exhaled breath carbon monoxide analysis at first antenatal care visit and at 28 weeks antenatal appointment.
		Proportion of women, identified as smoking or recent quitters at first antenatal care visit, who are provided with advice on the benefits of quitting.
		Proportion of women, identified as smoking, with documented referral to smoking cessation service (e.g. Quitline).
	Impact	Proportion of women, identified as smoking, with documented referral to smoking service who engaged with a smoking cessation service.
		Percentage of women who cease smoking between first antenatal care visit and birth
Element 2: improving detection and management of FGR	Process	Proportion of women with documented risk assessment for FGR at first antenatal care visit.
		Proportion of women (at any gestation) identified as at risk of FGR whose care was escalated as per the FGR care pathway^a^.
		Proportion of women with SFH measurement taken and plotted on growth chart at each antenatal visit from 24 weeks’ gestation.
		Proportion of stillbirths from 28 weeks’ gestation where substandard care for FGR detection or management are identified
	Maternity services impact	Proportion of term births with undetected FGR defined as severely growth restricted singletons (less than 3rd centile) undelivered at 40 weeks’ gestation (missed FGR)
	Outcome	Proportion of singleton babies delivered for suspected FGR at 37 weeks’ gestation or more who have a birthweight >25th centile.
Element 3: raising awareness and improving care for women with DFM	Process	Proportion of women provided with DFM information by 28 weeks’ gestation.
	Maternity services impact	Proportion of women with singleton pregnancies who have a CTG commenced within 2 hours of presenting (in person) at the maternity service with DFM, from 28 weeks’ gestation.
		Proportion of stillbirths from 28 weeks’ gestation where substandard care for DFM reporting or management are identified
		Percentage of women at 28 weeks’ gestation or more who attend a maternity service within 12hrs of DFM concern.
		Proportion of women with singleton pregnancies who present with DFM who undergo induction of labour or elective caesarean section before 39 weeks’ gestation for DFM as the only indication.
Element 4: improving awareness of maternal safe going-to-sleep position in late pregnancy	Process	Proportion of women who, by 28 weeks’ gestation, were given the information brochure on safe going-to-sleep position in late pregnancy.
	Impact	Proportion of women who report safe sleep practices after 28 weeks’ gestation.
		Proportion of women after 28 weeks’ gestation who can describe safe sleep practices (going to sleep on their side).
Element 5: improving decision making about the timing of birth for women with risk factors for stillbirth	Process	Proportion of women assessed for stillbirth risk factors at first antenatal care visit
		Proportion of women reassessed for stillbirth risk factors at 34-36+6 weeks’ gestation
	Impact	Proportion of women who report being involved as much as they wanted in decision-making about timing of birth
	Outcome	Proportion of women with singleton pregnancies who undergo induction of labour or elective caesarean section before 39 weeks’ gestation.

Abbreviations: *FGR* Fetal growth restriction, *SFH* Symphyseal-fundal height, *DFM* Decreased fetal movements, *CTG* Cardiotocography

^a^PSANZ/Stillbirth CRE FGR care pathway for singleton pregnancies [21]

**Impact measures** will assess the SBB programs effect on participants and include; healthcare professionals reported change in awareness, knowledge, attitudes, behaviours, and/or practices with implementation of the SBB and more broadly through use of the educational program; women’s reported change in awareness and behaviours in response to the five elements of care, as well as changes in experience with and quality of care received; maternity service reported change in service responsiveness and utilisation, Table 1.

**Outcome measures** focus on the endpoint effectiveness of the SBB program and demonstrate changes in clinical outcomes. The **primary clinical outcome** is stillbirth at 28 weeks’ or more gestation in singleton pregnancies without lethal fetal congenital anomalies. Secondary clinical outcomes will be collected from routinely collected perinatal data and include important maternal and new-born outcomes (including rates of obstetric intervention), Table 2.

**Table 2 Tab2:** Key clinical outcomes

Clinical Outcomes	Measure	
Primary outcome	Stillbirth at 28 weeks’ or more gestation in singleton pregnancies without lethal fetal congenital anomalies	
Secondary outcomes	Fetal/Neonatal	Stillbirth; 20 weeks’ or more gestation; 28 weeks’ or more gestation; 37 or more weeks’ gestation; associated with substandard care factors (undetected FGR, poor DFM reporting or management); cause specific (PSANZ classification^a^)
		Neonatal death; early (within 7 days of birth) or late (within 7-28 days of birth)
		Neonatal hypoxic ischaemic encephalopathy (mild, moderate, or severe grading- ANZNN criteria^b^)
		Small for gestational age; birthweight < 10^th^ centile; birthweight < 3^rd^ centile
		Neonatal seizures
		Preterm birth; early (birth before 32 weeks) or late (birth before 37 weeks)
		Early term birth (birth 37-38 weeks)
		Admission to nursery; special care and/or intensive care; length of stay
		Need for respiratory support (defined using ANZNN criteria^b^)
		Early and late onset neonatal infection (defined using ANZNN criteria^b^)
	Maternal	Induction of labour
		Caesarean section; elective; emergency (caesarean section birth after labour)
		Admission to intensive care
		Unplanned returned to theatre

^a^Perinatal Society of Australia and New Zealand (PSANZ) classification [30], ^b^Australian and New Zealand Neonatal Network (ANZNN) criteria [31]

**Economic measures** will evaluate incremental cost-effectiveness of the SBB compared to standard care, total and incremental costs to the health system, and total and incremental costs to society. Measures include all inpatient and outpatient health service utilisation from first antenatal booking to six weeks postpartum including antenatal ultrasound scans and maternal and neonatal length of stay from routinely collected administrative data sources.

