### The Safer Baby Bundle

The SBB is modelled on the SBLCB [15] with modifications made through extensive consultation with the project’s partners and collaborators, national experts, professional bodies, parent advocates and a survey of lead clinicians across Australian maternity hospitals [18]. The survey highlighted gaps in care for each of the proposed elements. The SBB, which is founded on evidence-based recommendations for Australia and New Zealand [19–24], aims to address these gaps.

The five SBB elements address commonly identified evidence practice gaps: 1) supporting women to stop smoking in pregnancy, 2) improving detection and management of fetal growth restriction (FGR), 3) raising awareness and improving care for women with decreased fetal movements (DFM), 4) improving awareness of maternal safe going-to-sleep position in late pregnancy, 5) improving decision making about the timing of birth for women with risk factors for stillbirth. Specific recommendations for the five elements are detailed in the SBB Handbook and Resource Guide [25], which has been endorsed by peak professional bodies, parent advocacy organisations, Departments of Health partners, and was made publicly available in October 2019.

Implementation of the SBB is supported by a comprehensive package of evidence-based and collaboratively developed resources. These include: best practice recommendations; implementation tools including clinical checklists and management algorithms; key performance indicators and audit; an educational program for healthcare providers (eLearning and face-to-face training); information and educational resources for women and their families; and a communications and awareness campaign.

In January 2019, the Stillbirth CRE, in partnership with the Stillbirth Foundation Australia, Still Aware and Departments of Health across Queensland (QLD), Victoria (VIC) and New South Wales (NSW), received funding to implement and evaluate the SBB across these three states. Commencing from mid-2019, implementation of the SBB was undertaken in partnership with these three state Departments of Health. Commencement dates, implementation strategies and approaches vary across jurisdictions but the intent for all is to progressively embed the SBB within existing care over a 12-24month implementation period (post-launching).

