## Methods

### Study aims and objectives

The overall purpose of this study is to determine the impact of implementing the SBB on Australian maternity services and perinatal outcomes. The primary aim is to (1) demonstrate the effectiveness of the SBB in reducing late gestation stillbirth rates (28 weeks’ gestation or more). The study also aims to: (2) understand the processes and contextual factors influencing implementation success; (3) determine the impact of the SBB on change in awareness, knowledge, behaviours and experiences around providing or receiving antenatal care for healthcare professionals and women respectively; (4) to undertake an economic evaluation of the SBB.

The study’s primary objective is to compare stillbirth rates at 28 weeks’ gestation or more across Australian maternity settings pre and post implementation of the SBB. Secondary objectives include:
Using routinely collected perinatal data to assess the endpoint effectiveness of the SBB for other important clinical outcomes, including any unintended consequences such as increased unnecessary intervention and preterm birthTo explore variations in the provision of antenatal care influencing disparities in stillbirth rates for Aboriginal and Torres Strait Islander, migrant and refugee, and rural and remote womenTo evaluate the coverage, acceptability, feasibility, fidelity, and sustainability of the SBB initiative and its implementation across settings and for different stakeholdersTo explore indirect process and contextual factors influencing antenatal care provision in relation to the SBB elements due to COVID-19 pandemic restrictions through interviews and surveys with project leadsTo explore the views and experiences of women and maternity healthcare professionals with antenatal care in relation to the five SBB elements utilising surveys, focus groups and interviewsTo estimate the cost-effectiveness of the SBB compared to standard care.

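### The DFM early-birth measure, and less so the suspected-FGR measure, can fall or stay flat while such births per singleton birth rise, because their denominators can grow with the bundle

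*Protocol article*

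**What the plan says.** Table 1 (Evaluation measures) contains two rows that concern birth brought forward for a specific reason.

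- Element 3, labelled a maternity services impact measure: the proportion of singleton women "who present with DFM who undergo induction of labour or elective caesarean section before 39 weeks’ gestation for DFM as the only indication". The denominator is women who present with DFM. No upper gestation limit is set on presentation.
- Element 2, labelled an outcome: "Proportion of singleton babies delivered for suspected FGR at 37 weeks’ gestation or more who have a birthweight >25th centile". The denominator is term singletons delivered for suspected FGR.

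The section on the Safer Baby Bundle lists the aims of the same two elements: "2) improving detection and management of fetal growth restriction (FGR), 3) raising awareness and improving care for women with decreased fetal movements (DFM"). A further Element 3 row tracks prompt attendance: "Percentage of women at 28 weeks’ gestation or more who attend a maternity service within 12hrs of DFM concern".

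Among the secondary objectives, the plan undertakes to use routine perinatal data to assess other clinical outcomes, including "any unintended consequences such as increased unnecessary intervention" and preterm birth. Two sets of measures that do not depend on DFM or suspected FGR bear on this. The first is the Element 5 outcome, "Proportion of women with singleton pregnancies who undergo induction of labour or elective caesarean section before 39 weeks’ gestation". The second is Table 2, which lists induction, elective caesarean, early term birth and "Preterm birth; early (birth before 32 weeks) or late (birth before 37 weeks").

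**The concern.** Both rows are to be compared before and after implementation, and both are conditional on a group whose size the bundle can be expected to change. More awareness of DFM should bring more women in, probably including some at lower risk. More attention to growth should lead to more births for suspected FGR. The article does not state that either group will grow, but this is a fair inference from the aims of Elements 2 and 3.

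When the denominator moves with the intervention, a proportion no longer tracks the number of births affected. The DFM row has an added flaw. A woman who first presents at 39 weeks or later is counted in the denominator but cannot have a planned birth before 39 weeks, so growth in late presentations alone lowers the proportion.

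The FGR row also starts at 37 weeks. A baby above the 25th centile delivered preterm for suspected FGR is therefore not counted by indication anywhere in the two tables.

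At stake is the reading of these two rows: whether Elements 2 and 3 led to more early births for DFM alone, or to more deliveries of normally grown babies for suspected FGR.

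**Working it through.** The article gives no baseline or target for either row, so there is no stated figure to reproduce. The check is ratio arithmetic on assumed inputs.

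**Inputs**
- 113,000 births per year at targeted sites (Sample size, Clinical outcomes), used as an approximation to singleton births.
- DFM share: about 500 of 2300 surveyed women (Survey data), 500/2300 = 21.7%. This is a share of expected survey respondents, not a presentation rate, so 10% is also tried.
- Assumed, not in the article: 5% of presenters have a DFM-only early birth; 3000 term deliveries a year for suspected FGR, 30% of them above the 25th centile; 20% baseline for the Element 5 measure; all growth factors.

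**DFM row.** If presentations grow by a factor g and DFM-only early births by a factor c, the measure changes by c/g and the rate per 1000 births by c. The measure falls or stays flat whenever c ≤ g, and the rate rises whenever c > 1. The baseline count is 113,000 × 0.217 × 0.05 = 1228.

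| g | c | Births | Measure | Per 1000 births |
|---|---|---|---|---|
| 1.5 | 1.2 | 1228 → 1474 | 5.0% → 4.0% | 10.9 → 13.0 |
| 1.5 | 1.5 | 1228 → 1842 | 5.0% → 5.0% | 10.9 → 16.3 |
| 2.0 | 1.5 | 1228 → 1842 | 5.0% → 3.75% | 10.9 → 16.3 |
| 1.2 | 1.5 | 1228 → 1842 | 5.0% → 6.25% | 10.9 → 16.3 |

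With a 10% DFM share, the first row becomes 565 → 678 births. The measure makes the same fall and the rate goes from 5.0 to 6.0 per 1000. The direction does not depend on the share. The last row shows that the measure rises when early births outpace presentations.

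**FGR row.** Let F be babies above the 25th centile and T those at or below it. The measure is F/(F+T). At baseline F = 900 and T = 2100.

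- Both × 1.5: 1350/(1350 + 3150) = 30.0%, unchanged, while F rises from 900 to 1350 (8.0 to 11.9 per 1000 births).
- F × 1.3, T × 1.5: 1170/(1170 + 3150) = 27.1%, a fall, while F rises from 900 to 1170.
- F × 1.5, T × 1.3: 1350/(1350 + 2730) = 33.1%, a rise.

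Masking therefore needs T to grow at least as fast as F. Adding only babies above the 25th centile pushes this proportion up, because each one enters the numerator as well. That makes the FGR row less exposed than the DFM row.

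**Would the Element 5 row show it?** Extra births from the DFM route = 113,000 × share × 0.05 × (c − 1). One year against one year, z = (extra/113,000)/√(2 × 0.20 × 0.80/113,000).

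- c = 1.2: 113 to 246 extra births for shares of 10% to 21.7%. The measure goes from 20% to 20.1–20.2%, z about 0.6 to 1.3.
- c = 1.5: 283 to 614 extra births. The measure goes to 20.25–20.5%, z about 1.5 to 3.2.

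The Element 5 row moves in the right direction, but a modest rise could be lost in it, and it cannot say which indication was responsible.

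**The case against.** The strongest reply is that the plan does not rest its harm monitoring on these two rows. The objective on unintended consequences, and the commitment to annual analysis under Data collection and management, both refer to routine data on all births. Element 5 and Table 2 measure early planned birth, preterm birth and early term birth without conditioning on DFM or FGR. This stands. A reader might infer that the evaluation as a whole could report stable or falling early birth while it was rising; the document does not support that. What is lost is the signal by indication.

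A second reply is that conditional proportions answer a proper question: once a woman presents, or FGR is suspected, do clinicians intervene more readily? For FGR, a falling share above the 25th centile can mean that suspicion has become more accurate. This also stands, and it is why the proportions should be kept. It does not make them a measure of how many births are affected.

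Third, the size of any masking is assumed. The article does not say how far either denominator will grow, and under other growth rates both rows rise. That is correct: masking is possible, not certain.

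Finally, the article allows its measures to be amended, and no decision rule is tied to these rows. That limits the consequence but leaves the definitions as they stand.

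**Conclusion.** The point holds for the two rows, not for the plan as a whole. It is clearest for DFM: the denominator can be expected to grow under Element 3 and includes women who cannot enter the numerator, so a flat or falling result does not exclude a rise in DFM-only early births per singleton birth. In the main illustration the measure falls by a fifth (5.0% to 4.0%) while the rate rises by a fifth (10.9 to 13.0 per 1000). For FGR it holds only if deliveries at or below the 25th centile grow at least as fast as those above it.

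Two stronger readings are tempting and neither is supported. One is that the rows must mislead; with faster growth in the numerator they rise as they should. The other is that preterm birth goes unmonitored; Table 2 covers it, though not by FGR indication.

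The conclusion rests on the inference that awareness and detection enlarge the two groups. Every numerical example uses assumed baselines and growth factors. This is a matter of how the measures are defined; no stated figure is wrong.

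**What to change.** 1. Keep both proportions, but limit the DFM denominator to women presenting before 39 weeks.
2. Add, for the same sites and periods, (a) planned births before 39 weeks for DFM alone and (b) term births for suspected FGR with birthweight above the 25th centile, each per 1000 singleton births.
3. Report the DFM presentation rate and the rate of birth for suspected FGR alongside, so that a change in either denominator is visible.
4. Where indication for birth is recorded, also report suspected-FGR births above the 25th centile before 37 weeks.
5. Read these rows together with Element 5 and Table 2, which stay as they are.

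The cost is a few more reported rows and a wording change in Table 1. The numerators in item 2 are those of the existing rows, and total births come from the routine extract. If a jurisdiction obtains these counts from audit samples rather than complete reporting, the sampling fraction is needed before dividing by all births. Item 4 is a new count. The article's list of requested perinatal data items does not name indication for birth, so its availability should be confirmed with the data custodians first.

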#### Non-identifiable electronic extract of routinely collected perinatal data

Approval will be sought through the relevant state perinatal data collection custodians to access and analyse routinely collected population-based surveillance system data covering all births in NSW, VIC and QLD public and private hospitals over the study time period (covering 15 years’ pre-implementation to 2 years’ post-implementation). This non-identifiable electronic data will be extracted from each of the participating jurisdictions at yearly intervals throughout the duration of the project.

Monitoring and timely reporting of any unintended harm as a result of SBB implementation, such as increased unnecessary intervention and preterm birth, is essential [32]. Annual analysis of routine data extracts throughout both implementation and maintenance phases will allow for benchmarking of selected indicators. Reporting of comparisons for stillbirth rates and other important clinical outcomes will be for both ‘targeted’ and ‘non-targeted’ implementers. These comparisons will describe the effect of state-wide uptake of SBB components over time and consider any indirect impacts on antenatal care provision due to COVID-19 restrictions by jurisdiction.

Requested data items include: maternal demographics and medical history; previous pregnancy complications and birth outcomes; current pregnancy details; labour and birth outcomes; neonatal outcomes; and hospital demographics. Routinely collected hospital service utilisation data for each participating hospital will also be obtained as part of the SBB dataset. These data are routinely collected and reported to state health departments as part of minimum reporting requirements for activity-based funding.

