#### Economic evaluation

A modelled health economic evaluation will be undertaken. The intervention costs will be obtained from the routinely collected health service utilisation data. In addition, health service and societal costs of stillbirth will be captured using publicly available data sources or data from peer-reviewed publications for women who have a stillbirth and those who do not, developed as a part of the Stillbirth CRE [1]. In partnership with the Stillbirth CRE the economic evaluation is being conducted by [name] from Monash University. The detailed protocol developed for this component of the evaluation will be published separately and is beyond the scope of this paper.

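### The six-week limit on economic resource use, read as written, cuts short the counted hospital stays of very preterm babies

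*Protocol article*

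**What the plan says.** The Economic measures paragraph under Evaluation measures promises the incremental cost-effectiveness of the bundle against standard care, together with "total and incremental costs to the health system, and total and incremental costs to society". It defines the resource use to be collected as "all inpatient and outpatient health service utilisation from first antenatal booking to six weeks postpartum", and the sentence continues "including antenatal ultrasound scans and maternal and neonatal length of stay from routinely collected administrative data sources". Neonatal length of stay is thus named inside a window that ends six weeks after birth.

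Under Study setting, the economic measures apply to all women attending for antenatal care at targeted sites. The restriction to 28 weeks or more is stated for the clinical outcome comparison and is not repeated for the economic population.

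The secondary objectives name preterm birth as a possible unintended consequence. The section on routinely collected perinatal data adds: "Monitoring and timely reporting of any unintended harm as a result of SBB implementation, such as increased unnecessary intervention and preterm birth, is essential". Table 2 lists birth before 32 weeks as a separate preterm outcome.

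The Economic evaluation section describes a modelled evaluation, takes intervention costs from routine utilisation data, and leaves the detailed methods to a protocol to be published separately.

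**The concern.** Six weeks postpartum is a natural end point for the mother. For a very preterm baby it can fall in the middle of the birth admission. If the window is applied by date to mother and baby alike, the last part of the longest neonatal stays drops out of the costing.

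The omission runs in one direction, because a closed window can only lower the counted cost of an early preterm birth. Preterm birth is also a harm that the study has undertaken to watch. If very preterm births became more frequent under the bundle, part of their cost would be missing and the bundle would look cheaper than it is. If they became less frequent, part of the saving would be missing. The incremental cost and the cost-effectiveness ratio are the quantities at risk.

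**Working it through.** **Inputs from the article.** The window closes at six weeks, or 42 days, after birth (Economic measures). Neonatal length of stay lies inside it (same sentence). The economic population has no lower gestation limit (Study setting). The six-week limit is a chosen value, so there is no formula behind it to reproduce.

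**Input assumed.** The article gives no lengths of stay. Discharge is therefore assumed at 34, 36, 38 or 40 weeks' postmenstrual age, to show the range. The arithmetic is for babies who stay in hospital from birth until that discharge.

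**Step 1: age when counting stops.** Postmenstrual age at the end of the window = gestation at birth + 6 weeks. A birth at 24 weeks gives 30 weeks; 26 gives 32; 28 gives 34; 30 gives 36; 32 gives 38; 34 gives 40.

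**Step 2: which stays are cut.** With G the gestation at birth and D the age at discharge, both in weeks, a stay is cut when D > G + 6, that is, when G < D - 6. Discharge at 34 weeks cuts births before 28 weeks; at 36, before 30; at 38, before 32; at 40, before 34.

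**Step 3: days not counted.** Stay = 7 × (D - G) days. Days lost = stay - 42, or zero if that is negative. For example, with birth at 28 weeks and discharge at 36, the stay is 7 × 8 = 56 days, the loss is 56 - 42 = 14 days, and 14/56 = 25%.

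| Birth (weeks) | Discharge 34 | Discharge 36 | Discharge 38 | Discharge 40 |
|---|---|---|---|---|
| 24 | 28 of 70 (40%) | 42 of 84 (50%) | 56 of 98 (57%) | 70 of 112 (62.5%) |
| 26 | 14 of 56 (25%) | 28 of 70 (40%) | 42 of 84 (50%) | 56 of 98 (57%) |
| 28 | 0 of 42 | 14 of 56 (25%) | 28 of 70 (40%) | 42 of 84 (50%) |
| 30 | 0 of 28 | 0 of 42 | 14 of 56 (25%) | 28 of 70 (40%) |
| 32 | 0 of 14 | 0 of 28 | 0 of 42 | 14 of 56 (25%) |
| 34 | – | 0 of 14 | 0 of 28 | 0 of 42 |

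Births before 28 weeks lose days in every column. Births at 28 to 33 weeks lose days only with later discharge. Births at 34 weeks or later lose none within this range.

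**Step 4: from a baby's stay to incremental cost.** Let n1 and n0 be the numbers of very preterm births per 1000 births with the bundle and with standard care. Let u1 and u0 be the mean uncounted days per such birth, and c the cost per day. The shortfall in incremental cost per 1000 births is c × (n1 × u1 - n0 × u0). It is zero if neither the number nor the uncounted stay changes, positive (favouring the bundle) if the product rises, and negative if it falls. The article supplies none of these terms, so the calculation stops here.

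**The case against.** The strongest reply is that the article only summarises the economic work. It calls the evaluation modelled and defers the detail to a separate protocol, which could extend the horizon or count whole any admission that begins within the window. The list of measures is also introduced as a non-exhaustive one, and no sentence says that an admission under way at day 42 is split. All of this stands, and it is why the point is conditional on reading the window as written. It does not remove the point: the article states an end date and names neonatal stay within it. A model fed with cut stays carries the cut forward unless later cost is added, and no such step is described.

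The second reply is that the harms at issue may be mostly late. The article's measures look at intervention before 39 weeks and at risk reassessment between 34 and 36+6 weeks. If added preterm births fall at 34 to 36 weeks, Step 3 shows no loss within the assumed range. This also stands, and it limits the likely size.

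Two stronger readings are tempting. Neither is supported.

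- A reader might see a contradiction with Table 2, which lists "Admission to nursery; special care and/or intensive care; length of stay" without a cap. That entry is an undefined clinical outcome, while the economic item is a costing input from administrative sources. The two would differ only if the cut were applied, and the uncapped entry does not show that it will be.
- A reader might infer that stillbirth is costed without limit while live birth is cut off, because "health service and societal costs of stillbirth will be captured using publicly available data sources or data from peer-reviewed publications". The same sentence goes on to cover women with a stillbirth and women without one, so it does not show one-sided treatment.

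**Conclusion.** The concern holds in a limited form. As worded, the six-week window ends before discharge for babies born before 28 weeks who go home at 34 weeks' postmenstrual age or later. It may do so for births at 28 to 33 weeks, depending on the discharge age. It does not do so from 34 weeks if discharge is by 40 weeks. The loss for an affected baby runs from 14 to 70 days in the cases tabulated, or 25% to 62.5% of that baby's stay. These figures rest on assumed discharge ages and describe a single stay; they are not percentages of incremental cost.

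A reader might go further and conclude that incremental cost is wrong whatever the bundle does, or that the costliest part of the preterm harm is left out. The documents do not support either statement. Incremental cost is distorted only if the number or the stays of very preterm births change, and the article gives no unit costs, numbers affected or expected shift at those gestations. The effect on the cost-effectiveness ratio is therefore unknown and may be small. The primary outcome, its power and the clinical monitoring of preterm birth are unaffected. Priority is minor.

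**What to change.** Keep six weeks postpartum as the limit for outpatient care and readmissions. For the birth admission, count the full stay of mother and baby, including transfers, to final discharge, even when that falls after six weeks. State this in the Economic measures paragraph and in the separate economic protocol. If that protocol already counts whole admissions, only the article's wording needs to be aligned.

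The cost is mainly a change of wording. The article already plans to obtain routine hospital utilisation data for each participating hospital. It does not list admission and separation dates, so their presence in the extract, and the ability to follow transfers, should be confirmed. The price in the analysis is a somewhat higher and more variable neonatal cost, because the longest stays are then counted in full.
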